#### Measurement of secondary outcomes

##### Neuromuscular adaptations of muscle mass and strength

Muscle mass and quality adaptations will be assessed daily prior to the first training session (~ 12 h from the last session) and 12 h after the last training session (T2) (until 12 h prior to the coma awakening), to the predicted death or ICU discharge. The muscle mass of the VL, *rectus femoris* (RF), and anterior tibial (AT) will be measured by MT and muscle quality, by echo intensity, both analyses obtained by ultrasound images. If the patient awakes from a coma and has the appropriate cognition to collaborate in active assessments, the global muscle strength will be evaluated by the Medical Research Council (MRC) score after 12 h of T2, in the ICU and at hospital discharge. Adequate cognition will be assessed by the absence of delirium after completing the Confusion Assessment Method for Intensive Care Units (CAM-ICU) score [52].

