**Methods:**

Thirty-nine patients will be assessed at baseline (T0–18 h of coma) and randomly assigned to the PM (control group), BFRp, or BFRpE groups. The training protocol will be applied in both legs alternately, twice a day with a 4-h interval until coma awake, death, or ICU discharge. Cardiovascular safety and applicability will be evaluated at the first training session (T1). At T0 and 12 h after the last session (T2), muscle thickness and quality will be assessed. Global muscle strength and physical function will be assessed 12 h after T2 and ICU and hospital discharge for those who wake up from coma. Six and 12 months after hospital discharge, physical function and quality of life will be re-assessed.

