### Sample size rationale

A total of 30 participants were used for the sample size calculation of the clinical trial [43]. Therefore, a sample of 39 patients will enable 10% sample loss for each experimental group (PM/control, BFRp, and BFRpE). Based on a recruitment average of 24 patients per month, 20% of non-consent and 30% of non-previewed death or immediate discharge, we aimed to recruit 7.2 patients per month. The recruitment in a single ICU will allow the study to be completed in a minimal period of 6 months.

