##### Physical function adaptations

Physical function will be assessed 12 h after T2 and in the ICU and at hospital discharge through the Physical Function in Intensive Care Test Scored (PFIT). Lastly, during home follow-up, functional motor performance of basic activities of daily living will be evaluated using the Barthel Index, 6 and 12 months after hospital discharge, by telephone.

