##### Quality of life adaptations

Quality of life will be measured simultaneously with basic activities of daily living performance, using the SF-36 questionnaire, which is validated in Portuguese and Brazilian culture and is reliably applicable by telephone [53, 54].

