## Statistical analysis

After data collection, participants will be distributed into subgroups by periods in coma (2, 3–4, 5–6 days), in alertness (1–2, 3–4, 5–6 days), and in ICU permanence (3–4, 5–6, 7–8, 9–10, 11–12 days). The normality of data will be analyzed using the Shapiro-Wilk test. One-way analysis of variance (ANOVA) will be used for intra-group comparisons in T0. A mixed-model analysis will be used for each dependent variable, whereas group and time will be considered as fixed factors and subject as the random factor. In case of significant *F*, the Tukey adjustment will be applied for multiple comparisons. In the event of a non-normal data distribution, a Kruskal-Wallis test will be applied to test for the differences in baseline values and the Friedman test to analyze the repeated measures. The adjusted *p* values will be calculated using the Hommel procedure [48]. Effect sizes between and within groups will be calculated using Cohen’s *d* [89]. The minimal clinically important difference will be assessed with distribution-based methods [90]. The statistical significance will be assessed at *p* < 0.05. All analyses will be performed using R 3.6.2 (The R Project for Statistical Computing, 2019) in R-studio 1.3.443 (RStudio Inc., Boston, MA, USA).

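### MRC, PFIT and follow-up Barthel and SF-36 are compared only among patients who wake or survive, so these secondary comparisons are not randomised comparisons and need labels, counts by arm and a ranked sensitivity analysis

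*Protocol article*

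**What the plan says.** All references are to the Protocol article.

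- **Objective.** The Secondary objective section confines function and quality of life to patients who survive coma in the ICU.
- **MRC strength.** Under Neuromuscular adaptations of muscle mass and strength, scoring is conditional: "If the patient awakes from a coma and has the appropriate cognition to collaborate in active assessments". The test is then named: "Adequate cognition will be assessed by the absence of delirium after completing the Confusion Assessment Method for Intensive Care Units (CAM-ICU) score".
- **PFIT.** The Abstract (Methods) gives the waking condition for strength and function together: "Global muscle strength and physical function will be assessed 12 h after T2 and ICU and hospital discharge for those who wake up from coma". The section on physical function adaptations does not repeat it and adds no delirium condition.
- **Barthel and SF-36.** Daily-living performance is to be "evaluated using the Barthel Index, 6 and 12 months after hospital discharge, by telephone". For SF-36, "Quality of life will be measured simultaneously with basic activities of daily living performance, using the SF-36 questionnaire". Baseline values of both come from the legal representative of each consented patient (Recruitment procedures).
- **Analysis.** "A mixed-model analysis will be used for each dependent variable, whereas group and time will be considered as fixed factors", with subject as the random factor (Statistical analysis).
- **Death.** The Abstract lists death among the events that end training. The Discussion allows the previous day's assessment to be used after unexpected death or discharge, and derives this from the daily muscle-mass measurements.

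**The concern.** Randomisation makes the three arms comparable as allocated. It does not make those who later wake, or who are alive a year after discharge, comparable across arms. If one arm loses more of its sickest patients, those remaining are on average fitter, and the arm can show better strength or function with no treatment effect on either. An arm that keeps frail patients alive or wakes more of them can look worse.

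The Background supplies reasons not to dismiss this. It reports that atrophy and weakness are associated with high mortality, so outcome and survival are plausibly correlated. It also says that cuff release may have cardiovascular effects not yet known, which might bear on recovery, so a difference between arms in survival or waking cannot be ruled out beforehand.

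The last-value rule does not help here. A patient who never woke has no MRC or PFIT score from the previous day, and someone who died before the 6-month call has no follow-up Barthel or SF-36 to carry forward.

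At stake are the study's hypotheses about strength, function and quality of life, and whatever use the planned later trial makes of those estimates.

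**Working it through.** **1. What each outcome is conditioned on**

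| Outcome | Condition in the text |
|---|---|
| MRC | awake and CAM-ICU negative |
| PFIT | awake |
| Barthel, SF-36 at 6 and 12 months | alive at the call |
| Barthel, SF-36 at baseline | none (by proxy) |

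Every condition in the first three rows arises after randomisation.

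**2. Numbers the plan itself gives**

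The Sample size rationale plans 39 patients, 39 / 3 = 13 per arm, with 10% loss per arm. That leaves 13 × 0.90 = 11.7, about 12 of 13 assessed. (Inflating 10 per arm for 10% loss gives 10 / 0.9 = 11.1, rounded up to 12, or 36 in all. The stated 39 is not reproduced, but nothing here depends on it.) The same section's "30% of non-previewed death or immediate discharge" is used to project the pace of recruitment. It is not mortality after randomisation, which the article does not give.

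**3. Size of the possible bias (assumptions labelled)**

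Assume no treatment effect on the outcome, that the least fit fraction d of an arm has no score, and that the outcome correlates ρ with fitness. The mean among those scored, in SD units, is

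m(d) = ρ φ(z_d) / (1 − d), where z_d is the normal quantile at d and φ is the normal density.

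With ρ = 0.5 (assumed):

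| d | φ(z_d) | m(d) |
|---|---|---|
| 10% | 0.1755 | 0.098 |
| 20% | 0.2800 | 0.175 |
| 30% | 0.3477 | 0.248 |
| 40% | 0.3863 | 0.322 |

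Spurious advantage of the arm with more losses:

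- equal losses: 0
- 30% vs 20%: 0.248 − 0.175 = 0.073 SD
- 40% vs 20%: 0.322 − 0.175 = 0.147 SD
- 30% vs 10%: 0.248 − 0.098 = 0.151 SD (from unrounded means)

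Sensitivity to the correlation, for ρ from 0.3 to 1.0: 40% vs 30% gives 0.044 to 0.147 SD, and 50% vs 30% gives 0.090 to 0.301 SD.

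**4. Against sampling error**

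With about 9 scored per arm (13 × 0.7 = 9.1), the standard error of a difference in means is about √(2/9) = 0.47 SD. A bias of 0.07 to 0.15 SD is then 0.07 / 0.47 = 0.15 to 0.15 / 0.47 = 0.32 standard errors.

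**5. Does ranking all patients behave differently?**

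In a simulation with 13 per arm, ρ = 0.5, no effect on the outcome, and 50% vs 30% not assessable, the arm with more losses had the better mean among those scored in 62% of trials, against 50% with equal losses. When patients without a score took the worst rank, the direction reversed: the probability that a patient in that arm ranks higher, minus one half, averaged −0.085.

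**The case against.** The strongest reply is that the article declares its target openly. The secondary objective concerns survivors, and rules for death and missing values commonly sit in an analysis plan, which is not at hand. That stands as far as it goes, and silence on missing data is not the point. The point rests on what the text fixes: a survivor-only objective, stated conditions for scoring, and a comparison of groups on the resulting values. Naming the population does not make its arms comparable.

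Other parts of the reply also stand. The bias is zero if losses are equal, and no passage shows that the arms differ in mortality. Table 1 selects patients with a predicted coma of 2 to 6 days and excludes severe cardiovascular instability, which should limit failures to wake. A ranked comparison answers a different question, and with 13 per arm a few chance deaths would move it.

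Several stronger readings are tempting but not supported:

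- **That all four outcomes need waking, absence of delirium and survival.** The delirium condition is stated for MRC only. Follow-up Barthel is not said to require waking, and its scale reaches 0 for complete dependence.
- **That 30% will die, leaving 9 of 13 per arm.** The 30% is a recruitment figure; the planned loss is 10%.
- **That the model is declared to treat death as ignorable.** The Statistical analysis section states no missing-data assumption.
- **That patients who never wake are expressly excluded.** The Discussion leaves patients outside the subgroups out of the analysis, and the alertness subgroups start at 1–2 days. A reader may infer exclusion, but the text does not say so of these patients.

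**Conclusion.** The point holds in limited form. Followed as written, the plan compares MRC, PFIT and follow-up Barthel and SF-36 between arms conditional on events after randomisation. Such a comparison can favour an arm with more deaths or failed awakenings.

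The illustrative size of 0.07 to 0.15 SD rests on an assumed correlation of 0.5 and assumed differences in deaths of 10 to 20 percentage points. The documents supply neither figure. A reader might infer that the trial's main conclusions are compromised; they are not. The primary cardiovascular measures are taken at the first training session and do not depend on later waking or survival. For secondary outcomes of a pilot this is a minor to moderate matter, worth correcting because the remedy is cheap.

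**What to change.** Keep the mixed model and make four additions:

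1. Label the MRC and PFIT results as conditional on survival and waking, and follow-up Barthel and SF-36 as conditional on survival.
2. Beside each result, report by arm the numbers dead, not awake and, for MRC, delirious.
3. Add, as a sensitivity analysis, a rank-based comparison of all randomised patients at each time point. For MRC and PFIT, death ranks lowest and alive but not awake or untestable ranks next. For Barthel, death ranks lowest.
4. Record vital status at the planned 6- and 12-month calls. Table 2 lists no mortality variable, and the article does not show that 12-month status is captured.

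The cost is analysis wording and one extra item at calls already scheduled. The downside is that the ranked result mixes survival with function and will be imprecise at 13 per arm. The tabulated counts let the reader see which component drives it.

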##### Physical function adaptations

Physical function will be assessed 12 h after T2 and in the ICU and at hospital discharge through the Physical Function in Intensive Care Test Scored (PFIT). Lastly, during home follow-up, functional motor performance of basic activities of daily living will be evaluated using the Barthel Index, 6 and 12 months after hospital discharge, by telephone.

##### Quality of life adaptations

Quality of life will be measured simultaneously with basic activities of daily living performance, using the SF-36 questionnaire, which is validated in Portuguese and Brazilian culture and is reliably applicable by telephone [53, 54].

#### Blinding procedures

To be considered a double-blind study, one of the authors will be assigned to create codes for the training-related adaptation data, in addition to being responsible for the randomization of patients. The evaluator, who evaluates the safety and training-related adaptations, will be blinded to the experimental groups. Each experimental group will be led by a different trainer who will also be blinded for the other training groups. Lastly, participants will be blinded by their coma, and in case the participant awakes from coma, information from the study will be provided, but not about the protocol they had previously undergone.

### Study interventions

#### Peripheral muscle training

After T1, in view of the cardiovascular safety and applicability of PM, BFRp, and BFRpE, training sessions will be held twice a day, divided by 4 h [51]. The starting training leg will be randomly chosen at T1 and, from that, alternated in every training session. Patients will undergo the experimental protocol if they present controlled temperature (between 36.5 and 37.5 °C), stable blood pressure (> 100 and < 150 of SBP and > 60 and < 100 of DBP), SpO_2_ > 90%, respiratory rate (RR) < 25 rpm, and HR > 60 and < 140 bpm [55].

##### Passive mobilization/control group protocol (PM)

The PM protocol will be modified from Barbalho et al. [37]. The authors applied 3 sets of 15 mobilizations for flexion and extension of the hips, knees, and ankles. Movement was standardized in 2:2 using a metronome (2 s flexion and 2 extension), totaling 3 min of PM. To standardize PM with the BFR protocol, in every minute of PM, 1 min of rest will be allowed, totaling 5 min of PM for each set. Following that, a 3-min rest will be allowed, and the mobilization will be repeated in 5 sets. The session will last 37 min on average [56].

##### Passive mobilization associated with blood flow restriction protocol (BFRp)

A pressure cuff with 17.5 cm of width and 94 cm of length (JPJ, Sao Paulo, Brazil) with a pressure manometer will be placed on the quadriceps muscle, on the inguinal fold. Afterward, a vascular Doppler probe (DV-600; Martec, Ribeirao Preto, Brazil) will be placed in the posterior tibial artery. To determine the occlusion pressure, the cuff will be inflated until the auscultatory pulse stops [57]. An external compression of 85% of the total vascular occlusion pressure will be applied for 5 min, followed by a 3-min rest (compression release) [42]. The BFR protocol will be synchronized to the PM protocol. Compression will be repeated 5 times during the training session, and occlusion pressure will be re-evaluated in all sessions.

##### Passive mobilization associated with blood flow restriction and combined with neuromuscular electrical stimulation (BFRpE)

The procedures for BFRp will be adopted and synchronized with an electrical stimulation protocol. For the electrical stimulation electrode placement, the skin will be subjected to trichotomy, abrasion, and asepsis. Rectangular-shaped electrodes (50 × 50 mm) will be placed on the distal and proximal motor points of the VL (proximal and distal points located between the reference line of the antero-superior iliac spine and the superior lateral border of the patella and on the line between the apex of the great trochanter and the superior lateral border of the patella, respectively), RF (located on the reference line between the antero-superior iliac spine and the superior patella border), and AT (on the line between the apex of fibular head and the medial malleolus). In addition to the reference lines, the placement of the electrodes demonstrated in Santos et al. [58] and Dirks et al. [59] will be used to guide the location and electrostimulation of VL, RF, and TA. Additionally, this electrode placement will be marked with a semi-permanent pen to maintain the stimulus points throughout the study. A biphasic electro stimulator (Dualpex 071, Quark Medical, Piracicaba, Brazil) will provide symmetric pulses of 100 Hz, pulses lasting 400 μs, 5 s on (0.75 s rise, 3.5 s contraction and 0.75 s decay), and 10 s off, the intensity must be capable of causing visible contractions. The mean intensities used should be maintained from 29 to 33 mA and increased in approximately 3 min, when muscle contraction is no longer visible. The session will last 40 min, including 30 min of stimulation, a 5-min warm-up, and a 5-min cool-down, both with 5 Hz of frequency, pulse wave lasting 250 μs, and sub-maximal intensities (without muscle contraction) [59, 60]. The same researcher will apply both the BFRp and electrical stimulation.

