### Muscle mass and quality assessment

#### MT and echo intensity (MT_echo_) by ultrasonography

MT and MT_echo_ will be measured by ultrasound images (Mysono U6 EX; Samsung Medison, Gangwon-do, South Korea). For body fluid homogenization, 15 min of rest in the supine position will be allowed, with the lower limbs neutrally positioned and sustained by a Velcro strip. A 7.5 MHz linear-array probe (LN5-12; Samsung Medison, Gangwon-do, South Korea), revested by surface gel, to promote acoustic coupling without dermic compression, will be placed longitudinally to the muscle fibers. The anatomic reference between two MT points of each muscle will be defined by the distal motor point sites used for the electrical stimulation. Additionally, for the VL, the anatomical reference will be the middle portion between the great trochanter and the lateral epicondyle [68]. For RF, the reference will be set at 50% and at two-thirds of the distance from the anterior superior iliac spine and the superior patella border [51, 69]. Anatomical references for AT will be defined in one-fourth of the distance between the inferior portion of the patella and the lateral malleolus and one-third of the distance between the border of the fibula and the medial malleolus [70]. Sequential images will be acquired with 6 cm of depth and, after digitalization, analyzed using the ImageJ software (National Institute of Health, USA). MT (cm) will be characterized as the perpendicular measurement between the superficial and deep aponeurosis [71]. MT_echo_ (A.U.) will be evaluated using greyscale grading, obtained by the histogram function of the software (0 = black and 256 = white) [72]. Three consecutive images of the same anatomic point will be analyzed, and the mean will be adopted as the final value for MT and MT_echo_ [73]. MT_echo_ will be normalized by MT (i.e., MT_echo_/MT, cm) to explain the effects of alterations on muscle size [57].

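### Skin preparation and lasting pen marks described only for BFRpE let the blinded evaluator recognise that arm when acquiring the ultrasound images

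*Protocol article*

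**What the plan says.** Four parts of the protocol article bear on this.

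- **BFRpE intervention.** "For the electrical stimulation electrode placement, the skin will be subjected to trichotomy, abrasion, and asepsis". Electrodes go on motor points of the vastus lateralis (VL), rectus femoris (RF) and anterior tibial (AT). The article adds that "this electrode placement will be marked with a semi-permanent pen to maintain the stimulus points throughout the study". The PM and BFRp sections describe no shaving, abrasion or marking.
- **MT and echo intensity by ultrasonography.** "The anatomic reference between two MT points of each muscle will be defined by the distal motor point sites used for the electrical stimulation". Bony landmarks are then given for all three muscles; for the VL, "Additionally, for the VL, the anatomical reference will be the middle portion between the great trochanter and the lateral epicondyle".
- **Neuromuscular adaptations of muscle mass and strength** (secondary outcomes). Thickness and echo intensity are measured daily before the day's first session, and again 12 h after the last session.
- **Blinding procedures.** "The evaluator, who evaluates the safety and training-related adaptations, will be blinded to the experimental groups". One author creates codes for the adaptation data and also handles randomization.

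**The concern.** Each of these provisions is reasonable alone, but they do not fit together. The person holding the probe works at or near skin that, as the article describes it, is shaved, abraded and inked in one arm only. Probe position, angle, contact pressure and the choice of images are settled at the bedside, before any coded file exists.

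Two consequences need to be kept apart. Knowing the arm at acquisition can shift the mean of BFRpE against the other two arms. That contrast carries the efficacy hypothesis, since the Background expects BFRpE to prevent atrophy and BFRp only to reduce it. A lasting landmark in one arm can make repeat scans there more reproducible, which changes the spread of the measurements and not their mean.

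Spread matters here because the Statistical analysis section plans within- and between-group Cohen's d and distribution-based minimal important differences. The abstract says the data will inform the design and sample size of a later trial. The article's own Discussion argues that high variability between measurements prevents detection of daily change.

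**Working it through.** The article gives no siting error and no SD by arm, so there is no stated figure to reproduce. The first part compares the text; the second is an illustration on assumed inputs.

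**Part 1: blinding at acquisition**

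1. Who carries the cues? Skin preparation and marks appear under BFRpE only, and the stated purpose of the marks is to hold the stimulus points, which exist only where there is stimulation.
2. Are the cues where the evaluator looks? Yes. The electrodes lie on the three muscles that are scanned, and the distal motor points are an ultrasound reference.
3. Are they present at the scan? T0 should be free of them, because VL thickness feeds the allocation and the first session follows T0. The daily scans and the one 12 h after the last session come later, and the marks are meant to last.
4. Does coding help? It can protect the later measurement in ImageJ. It cannot hide skin from the person acquiring the image.
5. What is revealed? BFRpE against the rest. The marks do not distinguish PM from BFRp.

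**Part 2: precision of change from T0**

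Assumptions: siting CV *u* = 5% without a mark; *m* = 2%, 3% or 4% with one; a true change of 5% in every arm; *s* = SD of true change between patients, 0% or 5%; and no marks in PM and BFRp. T0 is unmarked in all arms.

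- BFRpE: SD of change = √(u² + m² + s²)
- PM, BFRp: SD of change = √(2u² + s²)
- d = 5 / SD

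For m = 2%, s = 0: BFRpE √(25 + 4) = 5.39%, d = 0.93. Other arms √50 = 7.07%, d = 0.71. Ratio 7.07/5.39 = 1.31.

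For m = 2%, s = 5%: BFRpE √(29 + 25) = 7.35%, d = 0.68. Other arms √(50 + 25) = 8.66%, d = 0.58. Ratio 8.66/7.35 = 1.18.

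| m | d, BFRpE vs other (s = 0) | ratio | d, BFRpE vs other (s = 5%) | ratio |
|---|---|---|---|---|
| 2% | 0.93 vs 0.71 | 1.31 | 0.68 vs 0.58 | 1.18 |
| 3% | 0.86 vs 0.71 | 1.21 | 0.65 vs 0.58 | 1.13 |
| 4% | 0.78 vs 0.71 | 1.10 | 0.62 vs 0.58 | 1.07 |

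With s = 0 the ratio is √(2u²/(u² + m²)). It runs from 1 when the mark brings no gain (m = u) to √2 = 1.41 when the mark removes siting error altogether (m = 0), whatever the value of u.

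**The case against.** The strongest defence has five parts.

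- **Silence is not exclusion.** The article never says that probe sites go unmarked in PM and BFRp, and a condensed article may leave probe relocation to the full protocol. This stands against any firm claim of a relocation advantage. It does less against the blinding point: a common probe mark would not hide shaving, abrasion and electrode-point marks described for one arm.
- **Bony landmarks serve every arm.** This stands. They lessen any relocation advantage.
- **Acquisition is partly standardized.** Gel coupling without compressing the skin, a set probe orientation, a fixed 6 cm depth and the mean of three consecutive images are all specified. This narrows the room for influence but leaves judgement with an operator who can see the arm.
- **The outcomes are secondary.** This stands. The primary objectives are cardiovascular safety and applicability, and the marks do not affect them by this route.
- **Matching marks may not restore blinding.** Blinding procedures gives one evaluator both safety and adaptations, and cardiovascular measurements are taken during the T1 session, when cuff and stimulator are in use. If that person attends, the arm is seen anyway. This bears on the remedy, which has to cover T1 as well.

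A reader might also infer a far larger precision effect by treating both scans in a change as marked: √2 × 2% = 2.83% against √2 × 5% = 7.07%, so d of 1.77 against 0.71, a 2.5-fold gap. The documents do not support this for change from T0, because T0 is scanned before any electrode mark exists. Nor do they support reading better relocation as a bias in the mean.

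**Conclusion.** The point holds in a limited form. As written, the plan lets the evaluator identify BFRpE patients when acquiring images for muscle thickness and echo intensity, so the blinding statement is not met for acquisition in that arm. This rests on the text alone. The size and direction of any resulting bias cannot be derived from the article.

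The effect on precision is possible but modest. On the assumed CVs, within-group d for change from T0 would be about 0.93 against 0.71 with the same true change, roughly 1.3-fold, and about 1.2-fold once a 5% between-patient SD is added. It disappears if probe sites are in fact marked equally in all arms or if the bony landmarks relocate the probe as well as a mark would.

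**What to change.** At T0, before allocation, shave and mark the same VL, RF and AT probe sites in all three arms with the same pen. Renew the marks on one schedule and scan at those marks in every arm. Before the evaluator enters, remove electrode traces and cover abraded skin outside the probe site. Where existing staff allow, have someone other than the ultrasound evaluator take the T1 session measurements.

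Abrasion directly under the probe cannot be covered. If it stays visible, or if the steps above cannot be carried out, qualify Blinding procedures to say that image reading is blinded but image acquisition is not for BFRpE.

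The cost is a pen, a few minutes per patient and a short protocol addition, plus shaving and marking in patients who receive no stimulation. The study treatments are unchanged. Trial status reports that recruitment was suspended with too few participants, so later participants could still benefit.
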